### 1.1.2 Reduction of surface tension

Hutschenreuter showed that tyloxapol reduces surface tension (9). Wilde (18) also examined the influence of tyloxapol on the surface tension of sputum. He established that after adding tyloxapol before rotational viscosimetry, the surface tension values of the sputa fell significantly, namely up to  $\frac{3}{4}$  of their initial value.

### 1.1.2 Reduction of surface tension

Farber et al. (20) showed that tyloxapol also penetrates the mucous wall. Through moistening of the accumulations of mucus and mucus plugs, tyloxapol dissolves the viscous and dried secretion from the layer underneath it, thus enabling normal ciliary activity in the respiratory tracts.

### 1.1.3 Down regulation of inflammation

Tyloxapol inhibits activation of the transcription factor nuclear factor-kappa B (NK-kappa B), reduces resting secretion of the cytokine interleukin-8 (IL-8) in cultured human monocytes, and inhibits pro-inflammatory cytokines like lipopolysaccharide (LPS)-stimulated release of tumor necrosis factor-alpha (TNF-alpha), IL-1 beta, IL-6, IL-8, granulocyte-macrophage colony-stimulating factor (GM-CSF), and the eicosanoids thromboxane A2 and leukotriene B4 (21).

## 1.2. TOLARANCE OF TYLAXOPOL

Side-effects in the form of hypersensitivity reactions have only occurred very rarely. Nausea has occasionally occurred in allergic subjects. Occasionally, the first deep breaths may be followed by an initial urge to cough, which immediately disappears after moistening of the mucous membrane.

Hutschenreuter administered more than 1000 individual inhalations of Tacholiquin ® to 106 surgical patients. In doing so, he showed that Tacholiquin ® was very well tolerated by the patients. There were also no signs of intolerance in patients who inhaled tyloxapol several times a day over a period of 9 weeks (9).

In various studies, patients were treated continuously with tyloxapol for up to 4 years (in one case, it was administered in an aerosol tent every night for 4 years) with no side-effects being observed (10, 17, 22).

Segal et al (23) administered Tacholiquin ® continuously over 24 hours per day to children and adults with pertussis over a period of 7 days, and observed no side-effects (23).

Farber et al. (20) pointed out that tyloxapol is harmless, safe and effective in the treatment of patients with bronchiectases. According to the authors, tyloxapol facilitates the expectoration of sputum. In particular, the authors pointed out that tyloxapol caused no serious side-effects and is an ideal carrier for antibiotics, bronchodilators and substances with a vasoconstrictive action as a result of its chemical structure.

Camarata et al. (24) also established no adverse drug reactions after this active substance was administered to patients with atelectases.

There are no known interactions with other drugs.

### **1.3. RATIONALE**

The aim of the study is to assess the mucolytic effects of tyloxapol compared to saline (0.9%) in patients with chronic bronchitis (COPD).

## **2 OBJECTIVE OF THE STUDY AND ENDPOINTS**

### **2.1. OBJECTIVE OF THE STUDY**

Determine the magnitude of the effect of tyloxapol by means of lung function parameters, biomarker profiles in sputum and serum, and clinical symptoms and quality of life by standardized questionnaires [COPD activity index (CAT), Baseline Dyspnea Index (BDI) & Transition Dyspnea Index (TDI), St George's respiratory Quality of Life Questionnaire] will evaluated in response to tyloxapol ® vs. saline at day one and at end of treatment.

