### **2.3. SECONDARY AND EXPLORATIVE ENDPOINTS**

Secondary endpoints:

The analysis of symptom scores ((CAT, BDI,TDI and St George's respiratory Quality of Life Questionnaire), ease of sputum production by analog scale, lung function parameter (FVC, FEV1, MEF25, RV, RV/TLC), LCI will use the same methodology as that for the primary endpoint, using the ITT population. The analysis will include Day 1 and week 3 data. In addition acute changes of sputum weight on Day 1 at each treatment arm will be analyzed as described for the primary parameter.

Explorative endpoints:

Biomarker profiles (sputum cells, IL-1, IL-6, IL-8), in sputum will be analysed using an analysis of covariance (ANCOVA) model with covariates of baseline, smoking status and treatment. Estimated treatment differences along with corresponding 95 % CIs will be presented for the treatment comparison.

In addition anti-inflammatory activity of tyloxapol will be analyzed in vitro by the macrophage activation test.

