### **4 STUDY POPULATION**

#### **4.1. INCLUSION CRITERIA**

For inclusion in the COPD patients should fulfill the following criteria:

1. Provision of informed consent prior to any study specific procedures.
2. Female or male subjects aged 40-85 years inclusive at Visit 1.
3. Documented history COPD with a post-bronchodilator FEV1/FVC<0.70 and a post-bronchodilator FEV1<80% of predicted normal value at screening (spirometry will be used for this criteria assessment).
4. Current smoker or ex-smoker with a tobacco history of  $\geq 10$  pack-years (1 pack year = 20 cigarettes smoked per day for 1 year).
5. Women of childbearing potential (WOCBP) must use a highly effective form of birth control (confirmed by the Investigator).
  - Women <50 years old would be considered postmenopausal
6. At least a CAT value > 10 at Visit 1.

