#### 6.1.1. RECRUITMENT PROCEDURE

At Visit 1 before any assessment necessary for the study, the COPD patient will be informed by the physician according to the “Patient information” sheet. The patient will then give a written consent by signing the Patient Consent. As soon as the specific inclusion and exclusion criteria at Visit 1 have been checked, eligible patients will be assigned a randomization number in ascending order. They will then start double-blind trial treatment.

Additional visits can be scheduled and performed according to the investigators judgment of how to best manage the patient. At these visits in addition to recording any SAEs, AEs and concomitant medication use, a physical examination, vital sign assessment and lung function tests are to be performed.

Any unscheduled visits are to be recorded in the other clinical visits CRFs.

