### 6.2. **PROCEDURE BY VISIT**

#### 6.2.1. **METHODS AND MEASUREMENTS**

##### **Visit procedures at screening visit and before treatment phase A (Visit 1)**

- Patient information/Informed consent
- Date of visit
- Demographic data,
- Medical history and concomitant diseases
- Physical examination / Vital signs
- Concomitant medications
- Bodyplethysmography
- Bronchodilator response to Salbutamol
- Completing Questionnaires (CAT, BDI, St George)
- Inclusion/exclusion criteria

- Randomisation and drug dispensation
- Laboratory examination (including Urinalysis)
- Inhalation of blinded medication by nebuliser
- Sputum collection
- Recording side effects
- Recording “ease of expectoration”.
- Lung function monitoring up to one hour after sputum collection
- Lung clearance index one hour after inhalation
- Dairy explanation
- Appointment for the next visit

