**Visit procedures after end of treatment phase A at visit (Visit 3, day 21 ± 4 days)**

- Date of visit
- Physical examination / Vital signs
- Concomitant medications
- Bodyplethysmography
- Bronchodilator response to Salbutamol
- Completing Questionnaires (CAT and TDI, and St. George)
- Inhalation of blinded medication by nebuliser
- Sputum collection
- Recording side effects

- Recording “ease of expectoration”.
- Lung function monitoring up to one hour after sputum collection
- Appointment for the next visit after “Wash-out –phase”.

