### **Quality of life**

Quality of life measures were made using the St George's respiratory Quality of Life Questionnaire. Self-completed questionnaires were performed before and after each treatment phase. A clinically relevant change was considered to be 4 for total score. End-points included the global score change during active and placebo phases, as well as scores for the sub-scales of symptoms, activity and impact.

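### The Day 1 tyloxapol-versus-saline comparison of CAT, BDI and SGRQ cannot show a treatment response, because these scores are taken before the first inhalation of each phase

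*Protocol*

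**What the plan says.** **The comparison.** Section 2.1 states that lung function, biomarkers, CAT, BDI/TDI and SGRQ "will evaluated in response to tyloxapol ® vs. saline at day one and at end of treatment". Section 2.3 analyses the symptom scores by the primary endpoint's method in the ITT population and adds: "The analysis will include Day 1 and week 3 data". The synopsis, 7.1.2 and 9.4 repeat this for CAT, BDI and TDI. SGRQ is named in 2.1 and 2.3 but not in those three places. Section 9.4 speaks of secondary confirmatory analyses, and 9.5 makes no multiplicity adjustment.

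**The timing.** The Visit 1 list in 6.2.1 is headed "Visit procedures at screening visit and before treatment phase A (Visit 1)". It places "Completing Questionnaires (CAT, BDI, St George)" ahead of randomisation and the blinded inhalation. Inclusion criterion 6 is "At least a CAT value > 10 at Visit 1", and 6.1.1 says of patients found eligible and numbered: "They will then start double-blind trial treatment". The Visit 4 list is headed as preceding phase B and also puts CAT, BDI and SGRQ ahead of the inhalation. For SGRQ, the quality of life paragraph says: "Self-completed questionnaires were performed before and after each treatment phase".

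**End of phase.** Visit 3 has "Completing Questionnaires (CAT and TDI, and St. George)", and Visit 6 has the same three instruments.

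**Flow chart.** One combined row for BDI, TDI and St George is marked at Visits 1, 3, 5 and 6, and not at Visit 4.

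**The concern.** A Day 1 response to tyloxapol versus saline needs values taken after the phase's drug has been given. If a score is taken before the first inhalation, the label tyloxapol or saline on its Day 1 value names the drug the patient is about to receive. A difference between the labels is then either noise or something left over from phase A.

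Two consequences follow. A significant Day 1 result for one of these scores would be read as a rapid drug effect although none could have occurred. And if an effect of phase A tyloxapol did outlast the washout, it would be counted under saline.

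BDI has a further problem. In the visit lists it is never recorded on treatment, yet it is named among the scores compared between treatments.

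**Working it through.** The plan gives no figure for this comparison. Its sample size (9.3) concerns sputum weight and is not touched. No visit is labelled Day 1 (the flow chart calls the start Day 0), so Day 1 is read here as Visit 1 for phase A and Visit 4 for phase B.

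**Step 1: timing of each measure**

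| Measure | Visit 1 | Visit 4 | Basis |
|---|---|---|---|
| CAT | pre-dose | pre-dose | Visit 1: inclusion criterion 6 with 6.1.1 (firm). Visit 4: heading and list order |
| SGRQ | pre-dose | pre-dose | Quality of life paragraph (firm) |
| BDI | pre-dose | pre-dose | Headings and list order |
| Bodyplethysmography | pre-dose | pre-dose | List order |
| Sputum weight, ease of expectoration, lung function after sputum collection | post-dose | post-dose | Visit lists; for lung function also a flow chart row marked at all six visits |

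No questionnaire is listed after the first inhalation of either phase.

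**Step 2: what the Day 1 contrast estimates for a pre-dose score**

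Let π be a period shift from Visit 1 to Visit 4, and λT and λS the carry-over remaining at Visit 4 from phase A tyloxapol and phase A saline. The contrast is the tyloxapol-labelled value minus the saline-labelled value.

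- Tyloxapol first: Visit 1 − Visit 4 has expectation −(π + λT).
- Saline first: Visit 4 − Visit 1 has expectation π + λS.
- Mean over equal-sized sequences: (λS − λT)/2.

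The direct treatment effect does not appear.

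**Step 3: size, over assumed carry-over**

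The protocol gives no carry-over figure, so the values of λT below are assumptions, with λS = 0. The simulation used 20 patients, SD 2.41 and correlation 0.75 (sputum weight figures from 9.3, used only as a scale), an assumed period shift of 0.5, and 40,000 trials per row.

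| λT | Expected contrast | Simulated mean | Share with p < 0.05 |
|---|---|---|---|
| 0 | 0 | −0.001 | 4.2% |
| 0.3 | −0.15 | −0.149 | 5.0% |
| 0.6 | −0.30 | −0.299 | 8.1% |
| 1.2 | −0.60 | −0.601 | 19.9% |

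For comparison, values taken after the dose with a true effect of 1.2 and no carry-over gave a simulated mean of +1.199.

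On the SGRQ scale, taking a lower score as better: if 2 points of tyloxapol benefit persisted (λT = −2), the contrast would be (0 − (−2))/2 = +1, that is, worse under the tyloxapol label. This is a quarter of the protocol's own relevance threshold of 4.

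**Step 4: false positives without carry-over**

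Three scores (CAT, BDI, SGRQ) at unadjusted 0.05, if independent: 1 − 0.95³ = 1 − 0.857 = 0.143. Positive correlation between the scores lowers this.

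**Step 5: BDI and the flow chart**

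In the visit lists BDI appears only at Visits 1 and 4, and TDI only at Visits 3 and 6. BDI then has no on-treatment value, and TDI has no Day 1 value. By the flow chart, nothing in the combined row is collected at Visit 4, so no phase B Day 1 value of BDI or SGRQ exists and only CAT could be compared. The comparison fails on either schedule, for different reasons.

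**The case against.** The strongest reply is that Day 1 is only a baseline. The quality of life paragraph defines the SGRQ endpoint as score change during the active and placebo phases, and the spirometry paragraph uses baseline as a covariate. The sentence that Day 1 and week 3 data enter the analysis could mean that both feed a change score, with the model left to the statistical analysis plan promised in 9.4. For SGRQ this reading is possible. It does not fit section 2.1, which names a response at two separate times, nor BDI, which has no on-treatment value in the visit lists from which to form a change.

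A second reply is that list order is weak evidence. The Visit 1 list is not strictly chronological: laboratory tests and urinalysis come after randomisation, although exclusion criterion 9 depends on them. This stands, and it is why timing is called firm only for CAT at Visit 1 and for SGRQ.

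Three stronger readings are tempting and are not supported:

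- A reader might infer that the whole Day 1 objective fails, lung function included. It does not: lung function is recorded again after inhalation at Visits 1 and 4. What is missing is a statement of which reading is the Day 1 value, and whether RV and RV/TLC are repeated after the dose.
- A reader might infer that carry-over will distort the result. The protocol neither shows nor excludes persistence beyond the planned one-week washout. With complete washout the contrast is zero plus noise.
- A reader might count five lung function variables as well, giving 1 − 0.95⁸ = 34%. That assumes the pre-dose plethysmography is the Day 1 value, which the protocol does not say, and eight independent tests.

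**Conclusion.** The point holds for the questionnaires. As written, the Day 1 tyloxapol-versus-saline comparison of CAT, BDI and, in 2.1 and 2.3, SGRQ compares scores taken before the phase's drug and cannot show a response to it. Any systematic difference would be half the carry-over difference with reversed sign; without carry-over, any significant result is a false positive.

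The size is modest: up to three uninterpretable secondary tests, with a chance of at least one false positive of about 14% under independence. The conclusion rests on reading Day 1 as Visits 1 and 4, on equal-sized sequences, and, for BDI and for CAT at Visit 4, on headings and list order. The Day 1 objective remains attainable for the post-inhalation measures. A correction is worth making because the rule is stated in several places, produces a result that cannot be interpreted, and is cheap to change.

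**What to change.** - In the synopsis (statistical analysis), 2.1, 2.3, 7.1.2 and 9.4, limit the Day 1 treatment comparison to measures taken after inhalation: sputum weight, ease of expectoration, and lung function after sputum collection. Name that lung function reading as the Day 1 value.
- State that CAT and SGRQ at the start of each phase serve only as period baselines for the week 3 comparison.
- Keep BDI as the reference for TDI and remove it as an efficacy endpoint.
- Reconcile the flow chart row for BDI, TDI and St George with the Visit 4 and Visit 5 lists. If the flow chart stood, phase B would have no SGRQ baseline.

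The cost is wording in five places and the reconciliation of one flow chart row with the visit lists. No visit or measurement is added beyond those in the visit lists, the sample size does not change, and up to three tests that could not inform anyone are dropped.

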### **2.2. PRIMARY ENDPOINT**

The primary endpoint is sputum weight after 3 weeks of Tyloxapol– that after 3 weeks of saline treatment which will be analyzed for the Per Protocol Population. Estimated differences will be presented together with 95% confidence intervals (CIs) for the difference and two-sided p-values from a corresponding t-test.

### **2.3. SECONDARY AND EXPLORATIVE ENDPOINTS**

Secondary endpoints:

The analysis of symptom scores ((CAT, BDI,TDI and St George's respiratory Quality of Life Questionnaire), ease of sputum production by analog scale, lung function parameter (FVC, FEV1, MEF25, RV, RV/TLC), LCI will use the same methodology as that for the primary endpoint, using the ITT population. The analysis will include Day 1 and week 3 data. In addition acute changes of sputum weight on Day 1 at each treatment arm will be analyzed as described for the primary parameter.

Explorative endpoints:

Biomarker profiles (sputum cells, IL-1, IL-6, IL-8), in sputum will be analysed using an analysis of covariance (ANCOVA) model with covariates of baseline, smoking status and treatment. Estimated treatment differences along with corresponding 95 % CIs will be presented for the treatment comparison.

In addition anti-inflammatory activity of tyloxapol will be analyzed in vitro by the macrophage activation test.

### **3 STUDY DESIGN**

The study will be a monocentre, randomized, double-blind, crossover, placebo-controlled study in 24 COPD patients (including 4 Drop-out) in order to achieve 20 evaluable patients for the statistical analysis. 'Evaluable' mean eligible COPD patients having met all the inclusion and none of the exclusion criteria, having performed all scheduled clinical visits and with a "good" compliance as defined in section 7.5.

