| SAMPLE SIZE          | To be assessed for eligibility: $n = 26$ . To be allocated treatment: $n = 20$ for each treatment phase. To be analysed on per protocol basis: $n=18$                                                                                                                                                                                                                                                                                                                                                                                                                                                                                                                                                                                                                                                                                                                                                                                                                                                                                                                                                                                                                                                                                                                                                                                                                                                                                                                                                                               |

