**6.3. REPLACEMENT OF DROP-OUTS AND WITHDRAWALS**

It will be documented whether or not each patient completed the clinical study. If for any patient either study treatment were discontinued the reason will be recorded. Patients terminating the study prematurely will not be replaced. An estimation of 4 patients dropping out of the study has been considered when determining the number of patients to be recruited.

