### **9.3. SAMPLE SIZE CALCULATION**

The sample size is difficult to calculate. In a previous thesis of our group sputum weight was found to be of little variation at two separate time points in patients with asthma. After inhalation of hypertonic saline induced sputum of 20 asthmatics was  $4.9 \pm 2.41$  g and  $4.78 \pm 1.6$  g respectively.

These data are in keeping with a previous publication in chronic bronchitis with bronchiectasis. The authors found after inhalation of hypertonic a sputum weight of 5.3 g compared to 3.17 g after saline inhalation (24).

Therefore the calculated sample size of the present study is based on an expected difference for Tacholiquin ® in sputum weight of about 1.2 g corresponding to about 40% of that expected for saline with a standard deviation of  $s=1.7$  g roughly

corresponding to a correlation between sputum weights of  $\rho=0.75$ . Then a sample size of 20 achieves a power of 80%.

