#### **9.5. EXPLORATORY ANALYSIS OF EFFICACY CRITERIA**

All statistical tests will be two-sided using  $\alpha=0.05$ . An appropriate pooled center algorithm will be defined prior to unblinding the data. No adjustment for multiple testing will be done since the primary variable and the primary population is well defined.

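### The synopsis (20 allocated, 18 analysed) conflicts with Sections 3 and 6.3 (24 enrolled, 4 drop-outs, 20 evaluable); mixing the two would leave 16 patients and about 75% power

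*Protocol*

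**What the plan says.** The patient numbers appear in four places in the protocol.

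- **Synopsis, sample size row.** 26 patients are assessed for eligibility and 20 are allocated treatment in each phase. The row ends "To be analysed on per protocol basis: $n=18". The implied loss between allocation and analysis is 2.
- **Section 3.** The study is planned "in 24 COPD patients (including 4 Drop-out) in order to achieve 20 evaluable patients for the statistical analysis". Evaluable means eligible, with all scheduled visits performed and good compliance.
- **Section 6.3.** Patients who stop early are not replaced, and "An estimation of 4 patients dropping out of the study has been considered when determining the number of patients to be recruited".
- **Section 9.3, and the synopsis statistics row in the same terms.** The calculation rests on an "expected difference for Tacholiquin ® in sputum weight of about 1.2 g", "with a standard deviation of $s=1.7$ g roughly" "corresponding to a correlation between sputum weights of $\rho=0.75", and concludes "Then a sample size of 20 achieves a power of 80". Neither place says whether this 20 is the number allocated or the number evaluable.

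Sections 2.2, 7.1.1 and 9.4 assign the primary comparison to the per-protocol population. Section 9.5 sets the level: "All statistical tests will be two-sided using $\alpha=0.05".

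**The concern.** The number to randomise, the losses to expect and the number in the primary analysis are each given two values: 20 or 24, 2 or 4, and 18 or 20. They cannot be read as different populations. In a crossover every patient is allocated to both phases, so 20 per phase means 20 patients. Section 3's definition of evaluable is in substance a per-protocol definition, so 18 and 20 describe the same analysis set.

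The primary analysis is per protocol, so the evaluable count sets its power directly. A site working from the synopsis would stop at 20 randomised. If the losses then follow Sections 3 and 6.3, the analysis set falls below both stated sizes, and the rule against replacement leaves no way to make it up. The unlabelled 20 in the power sentence adds to the risk, because it equals both the synopsis's allocated number and Section 3's evaluable number.

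**Working it through.** **Inputs**

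- Difference d = 1.2 g and SD s = 1.7 g (Section 9.3).
- Two-sided α = 0.05 (Section 9.5).
- t-test on the within-patient difference (Section 9.4).
- 20 allocated and 18 analysed (synopsis); 24 enrolled, 4 lost and 20 evaluable (Section 3); 4 lost and not replaced (Section 6.3).

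**Step 1: what the 1.7 g is.** Section 9.3 ties it to a correlation of 0.75. The larger of the two single-occasion SDs printed there is 2.41 g. The SD of a paired difference with equal SDs is SD × √(2(1 − ρ)):

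2.41 × √(2 × 0.25) = 2.41 × 0.7071 = 1.70 g

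So 1.7 g is the SD of the paired difference and goes into the paired t-test unchanged.

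**Step 2: the plan's own figure.** Power comes from the noncentral t distribution with n − 1 degrees of freedom and noncentrality (d/s) × √n. At n = 20:

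(1.2/1.7) × √20 = 3.157, critical t (19 df) = 2.093, power = 84.9%

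The smallest n that reaches 80% is 18 (17 gives 78.0%). A sample of 20 therefore does achieve the stated 80%, with about 5 points to spare.

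**Step 3: power at each number of evaluable patients**

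| Route | Evaluable n | Noncentrality | Power (df n − 1) | Power (df n − 2) |
|---|---|---|---|---|
| Synopsis with its own loss: 20 − 2 | 18 | 2.995 | 80.6% | 80.3% |
| Section 3 with its own loss: 24 − 4 | 20 | 3.157 | 84.9% | 84.7% |
| Synopsis allocation with the loss in Sections 3 and 6.3: 20 − 4 | 16 | 2.824 | 75.2% | 74.7% |
| 24 enrolled, none lost | 24 | 3.458 | 91.2% | 91.0% |

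The n − 2 column is for a crossover analysis that also fits a period effect. It changes nothing of substance.

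**Step 4: how many to randomise if 4 are lost.** For 20 evaluable, 20 + 4 = 24, which is Section 3's figure. For 18 evaluable, 18 + 4 = 22, which is more than the synopsis provides.

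**Step 5: screening.** The synopsis screens 26 to allocate 20. At the same yield, 24 randomised would need 24 × 26/20 = 31.2, so about 32 screened. Leaving 26 in place would allow only 2 screening failures.

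**The case against.** The strongest reply is that the body of the protocol is coherent. Sections 3, 6.3 and 9.3 together give 24 enrolled, 4 lost and 20 evaluable, with at least 80% power, so only one synopsis row is out of line. The 75% figure takes its enrolment from one plan and its losses from the other, and no section states a plan for 16 patients. It also depends on rounded inputs: 40% of the 3.17 g saline value in Section 9.3 is 1.27 g, and with that difference 16 patients would give 79.7%. All of this stands. It makes the 75% a conditional risk and limits the severity, but it does not reconcile the two sets of numbers.

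Three stronger readings may tempt a reader, and the protocol does not support them.

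- **That the stated power fits neither plan once 4 drop-outs are applied.** Applied to Section 3 they leave exactly 20, where power is 84.9%. The synopsis's own 18 also clears 80%.
- **That the 80% belongs to 18 and is an error at 20.** Claiming 80% where the calculation gives 85% is conservative, and the inputs are given as approximate. An SD of 1.8 g in place of 1.7 g brings power at 20 to 80.7%.
- **That 1.7 g might be a per-treatment SD, giving about 99% power.** Section 9.3 rules this out through the correlation and the 2.41 g. A missing label on the SD is editorial.

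**Conclusion.** The point holds as an internal inconsistency: 20 allocated, 18 analysed and 2 lost in the synopsis, against 24, 20 and 4 in Sections 3 and 6.3. Neither plan is underpowered on its own numbers. The consequence is conditional: if 20 are randomised and 4 are lost, 16 remain and per-protocol power is about 75%, some 5 points below the 80% claimed.

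This rests on a true difference of 1.2 g, 1.7 g as the SD of the paired difference, a two-sided 5% paired t-test, and lost patients contributing nothing to the per-protocol comparison. The numbers should be reconciled because they govern when recruitment stops and how large the primary analysis is, but this is not a failure of the sample size calculation.

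**What to change.** Use one set of numbers throughout.

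1. Correct the synopsis sample size row to agree with Sections 3, 6.3 and 9.3: 24 randomised, 4 drop-outs, 20 evaluable per protocol. Adjust the number to be screened to match (about 32 at the synopsis's own yield).
2. In Section 9.3 and the synopsis statistics row, say that 20 is the evaluable per-protocol number and that power is about 85% on the stated inputs, and about 81% if only 18 are evaluable.
3. If 20 is instead the enrolment cap, choose one drop-out allowance, use it in every section, and state the power for the evaluable number that it leaves: about 75% at 16 with 4 losses, or about 81% at 18 with 2.

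Under the first route the cost is wording and restated figures. The endpoint, test and analysis population do not change, and the enrolment of 24 is already in Section 3.
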